After birth, women’s experience and satisfaction will be evaluated with a self-questionnaire within four days after delivery. Included women are also informed that they will receive another questionnaire by mail at 3 months postpartum. The questionnaire in the immediate postpartum period consists of questions about women’s current feelings and experience of cervical ripening, labor and birth. First, among women with DBC or dinoprostone insert, they will be asked to indicate the discomfort/pain and experience during the insertion of the device, and while the system was in situ. The levels of discomfort/pain assessments will be rated on a visual analogue score 1–10. Second, we will ask all women to indicate the feelings about the duration of IOL. Women will be asked to answer this question on a 10-point Likert-like scale (“0 = too long and unbearable” to “10 = acceptable”). The specific experience about IOL and the women’s overall satisfaction regarding IOL, labor and delivery will be also explored with a 10-point Likert-like scale (“0 = very dissatisfied” to “10 = very satisfied”) (Observational study 2). The last question will also explore whether women would prefer the same cervical ripening method again in a future pregnancy. Breastfeeding when leaving the maternity will be also reported.

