### Statistical analysis

Continuous data will be described by their means ± standard deviations and compared by t tests (or Mann-Whitney tests when appropriate), and categorical data will be described by percentages and compared by χ^2^ tests (or Fisher’s exact tests when appropriate). Maternal and perinatal outcomes will be compared according to cervical ripening method. For the analysis of dissatisfaction in immediate postpartum period, a score < 5 will be considered as a negative result and defined as “dissatisfied”. Maternal QOL at 3 months, assessed by use of EQ-5D-5L scores estimated with the most up-to-date preference-based value set [11,12], will be summarized in each group using mean ± standard deviations and compared between groups using mean differences (99% confidence index). In the five domains of QOL, we will dichotomise into women reporting problems versus reporting no problems and will calculate the outcomes for the different groups. The associations between women’s dissatisfaction at immediate postpartum period and poor QOL at 3 months post-delivery and the characteristics of their pregnancy, cervical ripening methods, labor, and delivery will be then assessed with a multivariate logistic regression model. All analyses were carried out using R software (version 4.0.2). P values <0.05 were considered to be statistically significant.

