## Discussion

This prospective observational study will include all women who will require cervical ripening whatever the method and the indication for IOL. It will assess data about the efficacy, safety, women’s experience of cervical ripening methods and health-related QOL at three months in different maternal and obstetric conditions and in different indications for IOL. The study will then identify factors associated with the efficacy (= vaginal delivery) of cervical ripening, safety, women’s experience and health-related QOL at three months. But, this database will also be used to analyze the efficacy, safety, and women’s experience of methods for cervical ripening in particular indication (gestational or fetal indication) or in particular women (previous cesarean delivery or obese)). We will expect to assess the “ideal” cervical ripening method in specific maternal and/or obstetric conditions. At long term, we also expect a better overall quality of life for the women after cervical ripening due to a personalized strategy.

The woman’s childbirth experience differs according to the type of labor (spontaneous or induced), the mode of delivery (vaginal route, cesarean section) and regarding parity [13]. In case of IOL, it is associated with less satisfaction compared to spontaneous labor [14]. Regarding woman’s experience during IOL, cervical ripening methods were questioned too [15–18]. In a secondary analysis of a randomized controlled trial that enrolled women undergoing IOL with oral misoprostol (n = 273, 54%) or Foley catheter (n = 229, 46%), experience of the duration of labor, pain during labor, general satisfaction with labor, and feelings of control and fear related to their expectation among term women were comparable between both groups. However, women in the Foley catheter group prefer more often to choose a different method for future inductions [18]. A French prospective cohort study including 94 hospitals and 3042 women who had an IOL showed that the determinants of maternal dissatisfaction were unbearable vaginal discomfort, insufficient pain relief during labor, lack of attention to the woman’s demands, a cesarean delivery and severe maternal complications [19]. These findings indicate the importance of advancing understanding of women’s perceptions of their childbirth experience during the perinatal period, specifically in case of IOL.

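### The only specified regression adjusts ripening method for labor and delivery, so its method coefficient leaves out any effect that runs through them; a model with pre-ripening covariates should be added

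*Protocol article*

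**What the plan says.** The Statistical analysis section of the protocol article describes three kinds of comparison.

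- **Tests by method.** Maternal and perinatal outcomes are compared across ripening methods with t, Mann-Whitney, chi-square or Fisher tests. No adjustment is stated.
- **EQ-5D at 3 months.** Scores are "compared between groups using mean differences (99% confidence index"). No adjustment is stated here either. For the five domains, "we will dichotomise into women reporting problems versus reporting no problems".
- **One regression.** It relates dissatisfaction, and "poor QOL at 3 months post-delivery", to a set of factors: "the characteristics of their pregnancy, cervical ripening methods, labor, and delivery will be then assessed with a multivariate logistic regression model". Dissatisfaction is binary: on the satisfaction scale, "a score < 5 will be considered as a negative result".

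Four other places bear on how the regression will be read.

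- The Introduction (section Rational) makes ripening method the exposure of interest for vaginal delivery, women's experience and QOL.
- Endpoints places vaginal delivery within the primary endpoint.
- The Discussion cites a French cohort in which the determinants of dissatisfaction included "a cesarean delivery and severe maternal complications".
- The Abstract (Methods and design) says that a significant multivariate result for a method, including on satisfaction and QOL, should lead to its use being reconsidered.

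**The concern.** Oxytocin use, the course of labor and the mode of delivery come after the choice of ripening method and may be partly caused by it. A model that holds them fixed asks how satisfaction differs between methods among women with the same labor and delivery. The study's question is how satisfaction differs when one method is chosen rather than another, including through its effect on delivery.

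Two consequences follow.

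1. The part of the method effect that passes through labor and delivery is removed from the coefficient.
2. If unmeasured factors influence both delivery mode and satisfaction, conditioning on delivery can create an association between those factors and method. That is collider bias, and its direction cannot be known in advance.

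At stake is the only specified adjusted estimate for method on satisfaction and QOL. A method that lowers satisfaction mainly by leading to more cesareans could look neutral in that estimate.

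**Working it through.** **Step 1: is delivery on the path from method to outcome?** The article supplies both links.

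- Method to delivery: the Introduction asks whether method raises the vaginal delivery rate, and Endpoints makes this the effectiveness measure.
- Delivery to satisfaction: the Discussion says that the childbirth experience differs by mode of delivery and names cesarean as a determinant of dissatisfaction.

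Delivery is therefore a mediator on the study's own premises.

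**Step 2: does another planned analysis give an adjusted total effect?** The tests by method and the EQ-5D mean differences have no stated adjustment. Method is left to the obstetrician's discretion, and the limitations in the Discussion accept that this can introduce selection bias. The article thus specifies a confounded unadjusted contrast and a model adjusted for post-exposure variables, with nothing in between.

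**Step 3: size.** The article gives no figure for this regression, so there is none to reproduce. All rates below are assumptions.

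*No direct effect.* Method A has 20% cesarean and method B 30%. Dissatisfaction is 10% after vaginal and 30% after cesarean delivery, whichever method was used.

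- A: 0.80 × 0.10 + 0.20 × 0.30 = 0.14
- B: 0.70 × 0.10 + 0.30 × 0.30 = 0.16
- Total OR = (0.16/0.84) / (0.14/0.86) = 1.17
- OR within each delivery mode = 1.00

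A stronger case has cesarean 15% v 30% and dissatisfaction 10% v 35% by delivery mode.

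- A: 0.85 × 0.10 + 0.15 × 0.35 = 0.1375
- B: 0.70 × 0.10 + 0.30 × 0.35 = 0.175
- Total OR = (0.175/0.825) / (0.1375/0.8625) = 1.33
- Delivery-adjusted OR = 1.00

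*With a direct OR of 1.3.* Dissatisfaction after vaginal delivery with method A is 10%, cesarean is 20% v 25-35%, and the cesarean-dissatisfaction OR is 2-5. Share removed = 1 − ln(1.3)/ln(total OR).

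| Cesarean, A v B | Cesarean-dissatisfaction OR | Risk, A v B | Total OR | Adjusted OR | Share of log-OR removed |
|---|---|---|---|---|---|
| 20% v 25% | 2 | 11.64% v 15.07% | 1.35 | 1.30 | 12% |
| 20% v 30% | 3 | 13.00% v 17.90% | 1.46 | 1.30 | 31% |
| 20% v 35% | 5 | 15.14% v 22.88% | 1.66 | 1.30 | 48% |

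The first and last rows are the extremes of the grid examined. The figures assume no unmeasured cause shared by delivery mode and satisfaction, so collider bias is not included.

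**Step 4: dichotomising (minor).** If the score were roughly normal, a cut at prevalence p would keep φ(z)²/[p(1−p)] of the information: 0.34 at p = 0.10 and 0.49 at p = 0.20. The article gives neither the distribution nor the prevalence.

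**The case against.** The best defence is that this is a determinants model. The Discussion says that the study will identify factors associated with experience and QOL, and the cohort it cites was a search for determinants of dissatisfaction. Labor and delivery variables belong in such a model, and the Statistical analysis section never calls the method coefficient the effect of choosing a method. This stands as far as it goes: the model need not be removed. It does not settle the matter, because the Abstract and Introduction draw conclusions about method, and no other adjusted model for satisfaction or QOL is specified.

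Stronger readings are tempting, but the article does not support them.

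- *The whole method effect is adjusted away.* Only the part through labor and delivery is. The Trial design and follow-up section collects discomfort or pain at insertion and in situ (for the balloon and the dinoprostone insert) and feelings about the duration of induction. These are plausible direct routes to satisfaction, and their contribution stays in the coefficient unless a labor variable also captures it. The examples ending at OR 1.00 assume no direct effect.
- *An association would go unreported.* The planned unadjusted comparisons would still show a contrast such as 14% v 16%, although confounded. That contrast is also small: with three equal groups of about 267 (800/3, assumed), power to detect it is about 10%.
- *Dichotomising is a major fault.* The cut at 5 is stated in advance, EQ-5D is also compared as a continuous score, and the 34-49% figures depend on an assumed normal score and prevalence.
- *The cut-off for poor QOL could be picked after seeing the data.* The article gives none, but an article may leave that detail to the full protocol or analysis plan, which is not shown.

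**Conclusion.** The point holds as a should-fix. Followed as written, the only specified adjusted coefficient for ripening method on satisfaction and QOL omits the effect that runs through labor and delivery, and may carry collider bias. That it omits this part follows from the article's own premises. How much is lost depends on assumed rates: all of the log-OR if method acts only through delivery (1.17 to 1.00 in the main example), and about 12-48% if there is also a direct OR of 1.3.

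The point is limited in scope. The regression does not cover vaginal delivery or morbidity, which are two of the three parts of the primary endpoint, and QOL is the secondary endpoint. The model is sound as a descriptive search for determinants. The weakness is that nothing separates that use from conclusions about method.

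**What to change.** 1. For the effect of method on satisfaction and QOL, specify a model with ripening method plus covariates fixed before ripening and already collected: for example BMI, previous cesarean, indication, Bishop score before ripening, gestational age at ripening and fetal presentation. Add parity, which the Introduction names as affecting results, if the database holds it. This model handles measured confounding only, and the report should say so.
2. Keep the model with labor and delivery variables, label it as a determinants analysis, and state that the method effect is not read from it.
3. Say in the text which model supports any conclusion that a method's use should be reconsidered.
4. Minor: in the method model, analyse the 0-10 scores as ordinal (for example by proportional odds) and the EQ-5D index as continuous. Keep the below-5 proportion as a descriptive summary.

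The cost is some wording and one extra model. No new data are needed.

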## Discussion

This prospective observational study will include all women who will require cervical ripening whatever the method and the indication for IOL. It will assess data about the efficacy, safety, women’s experience of cervical ripening methods and health-related QOL at three months in different maternal and obstetric conditions and in different indications for IOL. The study will then identify factors associated with the efficacy (= vaginal delivery) of cervical ripening, safety, women’s experience and health-related QOL at three months. But, this database will also be used to analyze the efficacy, safety, and women’s experience of methods for cervical ripening in particular indication (gestational or fetal indication) or in particular women (previous cesarean delivery or obese)). We will expect to assess the “ideal” cervical ripening method in specific maternal and/or obstetric conditions. At long term, we also expect a better overall quality of life for the women after cervical ripening due to a personalized strategy.

The woman’s childbirth experience differs according to the type of labor (spontaneous or induced), the mode of delivery (vaginal route, cesarean section) and regarding parity [13]. In case of IOL, it is associated with less satisfaction compared to spontaneous labor [14]. Regarding woman’s experience during IOL, cervical ripening methods were questioned too [15–18]. In a secondary analysis of a randomized controlled trial that enrolled women undergoing IOL with oral misoprostol (n = 273, 54%) or Foley catheter (n = 229, 46%), experience of the duration of labor, pain during labor, general satisfaction with labor, and feelings of control and fear related to their expectation among term women were comparable between both groups. However, women in the Foley catheter group prefer more often to choose a different method for future inductions [18]. A French prospective cohort study including 94 hospitals and 3042 women who had an IOL showed that the determinants of maternal dissatisfaction were unbearable vaginal discomfort, insufficient pain relief during labor, lack of attention to the woman’s demands, a cesarean delivery and severe maternal complications [19]. These findings indicate the importance of advancing understanding of women’s perceptions of their childbirth experience during the perinatal period, specifically in case of IOL.

The woman’s childbirth experience may impact the future health of women and their children. A positive experience may lead to a sense of accomplishment and to a sense of dignity and self-confidence for the woman. A negative childbirth experience may rise to maternal distress, helplessness, even postpartum depression or post-traumatic stress disorder [20–23]. In addition, the woman’s childbirth experience also affects their early interactions with the child [24,25]. To our knowledge, no published study has evaluated the women’s satisfaction in the immediate postpartum period and the quality of life at long-term regarding various cervical ripening methods, maternal and obstetric conditions and various indications for IOL. The present study will seek to answer these important questions.

Strengths of our prospective observational study include its examination of cervical ripening for variety of maternal, fetal and elective indications at one tertiary hospital. All women with cervical ripening in our center will be cared for by the same obstetric team throughout the period of study, which especially avoided significant variation regarding diagnosis of maternal or obstetric diseases, parameters for cervical examination and IOL management, and obstetric intervention. This will allow for standardized protocols to be followed, thus mitigating differences in outcomes due to variations in clinical practice, increasing the generalizability of our findings. For example, cervical ripening is regularly used in women with one previous cesarean delivery in France [26–28]. In our team, women with one previous cesarean delivery are not contraindicated to mechanical device and its practice is usual and well framed [29]. Other strengths also include performance of individual and prospective collection of data throughout the study period by the same physician and using a standardized protocol according to Bishop score (systematic cervical ripening for IOL with an unfavorable cervix (Bishop score <6), repeating cervical ripening until Bishop score will be above 6). These methodological choices (monocentric design, very large inclusion criteria, outcome, sample size, questionnaires…) are guided by a pragmatic view about cervical ripening, such as all large prospective observational studies in obstetrics [30–33]. These studies allow multiple analyses of data and conclusions about pragmatic management and consequences of some current obstetric conditions that were not adapted to randomized controlled trials (i.e., twins with The JUmeaux MODe d’Accouchement (JUMODA) study) [30,34–39].

Nevertheless, the study presents certain limitations. First, the choice of the method of cervical ripening (DBC, vaginal dinoprostone insert or oral misoprostol) will be left to the free discretion of the obstetrician responsible for the woman at the beginning of IOL. That can introduce selection bias if participants regarding cervical ripening methods differ in important ways other than outcome. Second, our research will be not blinded, it is not possible to blind women and medical staff due to the nature of the intervention (e.g., CRB vs. vaginal dinoprostone insert vs. oral misoprostol), that may affect the physician’s strategy when choosing a follow-up plan. Third, the single-center design of the study will only allow us to conclude on our practice, and it will be difficult to extrapolate our results except among teams with the same practices as us. Fourth, it might also be interesting to analyze a potential economic impact with the consumption of several medication, analgesics and an increase in the hospital staying, specifically in case of consecutives methods. These secondary analyses were not originally planned, but should be done using registered data.

## Conclusions

This study will reveal that some cervical ripening methods will be more effectiveness, safe, with good women’s experiences and QOL at 3 months compared to others regarding maternal and obstetric characteristics.
